## Abstract

**Background:**

Latina teens experience sexual and reproductive health disparities; however, few effective interventions designed for Latina teens and their families exist. Floreciendo is a sexual and reproductive health intervention for Latina teens (14–18 years) and their female caregivers (e.g., mothers, sisters), delivered by trained staff at community partner organizations (CPOs).

**Methods:**

This protocol describes a hybrid type 2 mixed-methods study with a pilot 2^3^ factorial experimental design which draws on the multiphase optimization strategy (MOST) framework. Small groups of teen-caregiver dyads (target n = 92 dyads/184 participants) will be randomized to 1 of 8 conditions across four CPOs. All will receive the Foundations in Sexual Risk Prevention (i.e., constant) component. Groups of dyads will be randomized to different combinations of three intervention components of Floreciendo, which are either “on” or “off”: 1) Condoms and Contraception, 2) Family Strengthening, and 3) Gender and Relationships. Our aim is to examine the feasibility of using a factorial design and the acceptability of the intervention components. We will also explore effectiveness outcomes—including risky sexual behavior (primary) and incidence of sexually transmitted infections and unplanned pregnancy (secondary)—and implementation outcomes, including appropriateness, feasibility, adoption, sustainability, cost, and fidelity. Qualitative data will build on quantitative data. We will conduct focus group discussions and key informant interviews with Latina teens, female caregivers, facilitators, CPO leadership, and collaborators.

**Discussion:**

Results will be used to guide intervention component and implementation refinement and will inform plans to conduct a fully powered optimization trial of Floreciendo.

## Background

1

Latina teens face a disproportionate burden of STIs, including HIV, and other adverse effects of risky sexual behavior. Compared to their White counterparts, Latina teens have higher rates of syphilis, chlamydia, gonorrhea, and HIV/AIDS [1], lower rates of effective birth control at last sex [2], and more than double the rate of teen pregnancy [3]. Latina teens also have high rates of mental health challenges [4], intimate partner violence (IPV) [5,6], and risky substance use [7,8]. These health disparities are influenced by unique contextual factors facing Latina teens and their families, including acculturation, language barriers, immigrant status, religion, and cultural norms (e.g., machismo) [9].

Parents influence the sexual behavior of their teens, and positive parenting practices (e.g., monitoring, open parent-child communication) can deter teens' risky sexual behaviors [10]. More frequent mother-daughter communication about sex is associated with teens' improved beliefs in taking responsibility for contraceptives, as well as confidence in and frequency of communicating with partners [[11], [12], [13]]. Sexual health interventions for Latine teens and their family members have shown positive effects on parent-teen communication and teens’ sexual behavior [[12], [13], [14], [15], [16]]. However, a scoping review conducted by our team identified no existing evidence-based sexual and reproductive health interventions for Latina teens and their female caregivers specifically (publication forthcoming).

Floreciendo is a sexual and reproductive health intervention for Latina teens and their female caregivers comprised of four 2-h sessions. Over two years, our team adapted Floreciendo [[14], [17], [18]] from IMARA, an evidence-based mother-daughter intervention for Black families [15,16]. While a traditional approach would involve piloting and assessing the intervention as a package [19,20], we were interested in unpacking the “black box” of Floreciendo. Specifically, we wished to assess which of its intervention components impact teens’ sexual and reproductive health outcomes, independently and in combination with each other. Our approach was shaped by the multiphase optimization strategy (MOST) framework, which guides the development and optimization of a multi-component intervention that produces the best expected outcome within key constraints imposed by the need for efficiency, affordability, and/or scalability [19,20]. The MOST framework includes three phases focused on preparing, optimizing, and evaluating the intervention. Piloting the intervention and the experimental design selected for the eventual optimization trial is a critical activity in the preparation phase [19,20].

This study protocol describes a pilot optimization trial of Floreciendo. Reflecting the purpose of the preparation phase in MOST, our aim is to examine the feasibility of using a factorial design and acceptability of the intervention components to inform the subsequent optimization and evaluation phases via a fully powered optimization trial. We also seek to explore effectiveness outcomes, implementation outcomes, mediators, and proximal behavioral outcomes to inform intervention component refinement and future implementation. This study uses a community-based participatory research (CBPR) approach [21], guided by the Floreciendo Community Advisory Council, made up of representatives from community partner organizations (CPO), researchers, Latina teens and female caregivers, and other experts in Latina health. For this paper, we drew on the SPIRIT guidelines for reporting on clinical trials [22] and guidelines for reporting on preparation phase activities of the MOST framework [23].

## Methods

2

### Study design

2.1

This is a hybrid type 2 effectiveness – implementation mixed methods study and uses a 2 × 2 × 2 (or 2^3^) factorial experimental design for the pilot optimization trial. We chose a hybrid type 2 design given that we aim to run a fully powered optimization trial with equal interest in effectiveness and implementation outcomes [24] and given that we adapted Floreciendo from an evidence-based program [15,16]. We chose to pilot a factorial trial design given our ultimate goal of optimizing the Floreciendo intervention using the MOST framework [19]. We decided on a mixed methods approach to facilitate a deeper understanding of exploratory effectiveness and implementation outcomes than would be possible with either method alone [25].

All dyads of Latina teens and their female caregivers receive the first of the four intervention sessions of Floreciendo (i.e., the “constant,” Foundations in Sexual Risk Prevention). Dyads are randomized to receive different combinations of the remaining three sessions which are either delivered (i.e., “on”) or not delivered (i.e., “off”): Condoms and Contraception, Family Strengthening, and Gender and Relationships. The study design therefore includes eight experimental conditions. Sessions are led by trained staff at each CPO. To facilitate easier communication about the conditions and enhance adherence to condition delivery [26], our Community Advisory Council chose to name each condition after a popular food in Latine culture, on a scale from most complex (i.e., chilaquiles) to simplest (i.e., maiz) (Fig. 1). In using a factorial design, there is no typical control condition; that is, participants are used in the estimation of all main effects and interactions [27].

**Fig. 1 fig1:**
[figure not shown]
Conditions and planned number of Floreciendo workshops.

We plan to enroll about 92 dyads (ñ184 participants total). Floreciendo is designed to be delivered in small groups of roughly 3–5 dyads. To achieve our planned sample size, we expect to deliver about 24 workshops. Our optimization objective [20] is to arrive at the best expected outcome among all active conditions (i.e., with no time or cost restrictions on the number of factors which can be “on”). This objective was determined through our formative Floreciendo research, whereby no specific constraints (i.e., limitations on cost or time) for delivering the intervention were raised by Latina teens, female caregivers, or CPO staff/leadership [17]. We will collect qualitative data after collecting quantitative data, with greater emphasis placed on the quantitative data (i.e., using a QUANT → qual design) [25].

### Setting and partners

2.2

The study setting is the Chicagoland area, where Latines represent the second largest racial/ethnic group and comprise one-third of the region's population [28]. This study is being conducted through a partnership between the Center for Dissemination and Implementation Science at the University of Illinois Chicago (UIC) and four CPOs: 1) Expanded Mental Health Services of Chicago (EMHS), which includes two community-funded mental health centers (The Kedzie Center and the LoSAH Center of Hope); 2) Centro Romero, a social service organization serving Latine refugee and immigrant communities on the North side of Chicago; 3) Corazon Community Services, a social service organization serving Latine families in Cicero, Illinois; and 4) The Gads Hill Center, a social service organization serving children and their families on the West side of Chicago. The Floreciendo Community Advisory Council, launched at study conception [14], meets bi-monthly and provides guidance on all aspects of the study.

### The floreciendo intervention and its components

2.3

Floreciendo, meaning “blooming” in Spanish, is a sexual and reproductive health intervention designed for Latina teens (aged 14–18 years old) and their female caregivers (e.g., mothers, sisters, aunts, grandmothers) generated using systematic process based on existing literature [14]. It aims to reduce risky sexual behavior to prevent STIs and unplanned pregnancy, while promoting mental health and reducing IPV and risky substance use. In line with the IMARA program, Floreciendo draws on the social personal framework [29], recognizing multiple levels of influence on teens’ sexual and reproductive health from individual, social, and environmental factors.

In interactive workshops conducted in-person at CPOs, teens and caregivers engage in joint and separate activities. All sessions begin with joint introductory activities in the same space. Then, dyads are separated for teens and caregivers to learn parallel content without judgment. Finally, dyads return to the same space for joint closing activities. Participants indicate their preferred language (English or Spanish) at the beginning of the first session. If all teens and/or caregivers agree on a language, that language is used throughout. If there are different levels of comfort with language, simultaneous translation is used. The workshop emphasizes strong teen-caregiver relationships and seeks to build motivation for protection from sexual health risks, while strengthening caregivers’ credibility as a resource for reducing sexual risk behavior.

Floreciendo is made up of four 2-h sessions, each addressing a topic believed to support sexual and reproductive health decision-making:•*Foundations in Sexual Risk Prevention:* Covers key topics in sexual and reproductive health and helps teens and caregivers develop an awareness of sexual behavior risks.•*Condoms and Contraception:* Teaches different forms of condoms and contraception and offers experiential activities on using them.•*Family Strengthening:* Facilitates learning and practice in how teens and caregivers can communicate about sex and addresses family norms and expectations in Latine culture.•*Gender and Relationships*: Shares what a healthy relationship is and how to recognize IPV and discusses how gender and cultural norms in Latine culture influence teens' sexual behavior.

### Conceptual model

2.4

Our conceptual model depicts the links between the intervention components and reductions in risky sexual behavior (primary distal outcome) and STI incidence and unplanned pregnancy (secondary distal outcome). Each component addresses one proximal mediator, which is linked to the desired distal outcomes through one or more proximal behavioral outcome (Fig. 2).

**Fig. 2 fig2:**
[figure not shown]
Conceptual model depicting links between intervention components and desired outcomes.

### Eligibility criteria

2.5

We are enrolling Latina teens and their female caregivers, defined as an influential adult female in the teen's life (e.g., mother, sister). To be eligible, teens must identify as Latina and be 14–18 years old. Caregivers must be a female caregiver of a Latina teen aged 14–18 years old and be 19 years old or older. Teens and caregivers must speak English and/or Spanish, be living with or in daily contact with each other, be available to simultaneously participate in the workshop and research activities, and agree to participate as a dyad. Teens and caregivers are excluded if they are unable to provide informed consent/assent or if they participated in the theater testing that informed this pilot optimization trial [18].

### Randomization and masking

2.6

Given the large number of conditions [30], the randomization schedule is generated prior to the study start by the study statistician and organized in Excel. Groups of dyads are randomly assigned to 1 of 8 conditions (Fig. 1) in blocks of 8. Conditions are revealed line by line as the recruitment of each group of dyads occurs. The Floreciendo Project Director manages the randomization schedule and communicates assignments to CPO sites. Each CPO has an equal chance of delivering any condition, and each intervention component will be delivered a roughly equal number of times by the study end. Facilitators at each CPO are trained in delivering all intervention components given the relatively small sample size, as it would not be feasible for each CPO to deliver all eight conditions.

CPO and UIC staff are blinded to the condition when approaching and recruiting participants. Only key UIC staff, facilitators, and CPO supervisors are aware of the condition for the purposes of delivering the workshop and are informed not to disclose the condition to participants prior to the workshop. Teens and caregivers are informed of their condition just before the workshop starts and are asked not to discuss their condition assignment with anyone outside of their group. To measure possible contamination, participants are asked on follow-up surveys the extent to which they discussed content received in their condition with participants randomized to other conditions.

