### Procedures

2.7

CPO staff and/or UIC study staff approach potential participants using an interest form which collects contact information. UIC study staff recruit potential participants by confirming eligibility, gathering informed consent, and registering them for a workshop. Groups of participants are randomly assigned to complete 1 of 8 intervention workshop conditions at a CPO site for 1 or 2 days (Fig. 3). All receive the constant component. Groups randomized to receive one additional component attend a one-day workshop, and groups randomized to receive two or more additional components attend a two-day workshop (see conditions in Fig. 1). Each participant receives between $100 and $220 depending on the condition they are randomized to and whether selected for a focus group discussion. Compensation includes $25 for each workshop session attended; our formative research highlighted the importance of compensating participants for their time attending sessions, not just completing assessments [17]. Compensation also includes $5 to cover transport for study activities [17].

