### Analyses

2.15

We will assess the feasibility of using a factorial design and acceptability of intervention components using descriptive statistics. To explore effectiveness outcomes in support of our move towards running a fully powered optimization trial, we will conduct an intention-to-treat analyses. We will use mixed-effects models for continuous outcomes and generalized estimating equations for binary outcomes. We will examine the mean difference in risky sexual behavior scores (primary outcome) for each intervention component from baseline to follow-up. Where sample sizes allow, we will do the same for STI incidence and unplanned pregnancy. Each experimental factor will be coded at two levels using effect coding (“on” = 1; “off” = −1) [19]. We will replicate analyses to look at component effects on theoretical mediators and proximal behavioral outcomes and explore the possibility of examining mediation effects and interactions between components.

For exploratory implementation outcomes, we will conduct descriptive analyses to summarize quantitative measures from participant and facilitator/staff/collaborator implementation surveys, as well as the facilitator and observer fidelity forms. We will use the *planning for and assessing rigor in rapid qualitative analysis (PARRQA)* rapid qualitative analysis framework [46] to analyze open-ended responses, focus group discussion transcripts, and key informant interview transcripts. Data will be sorted using a matrix, with relevant data extracted and key themes refined through extensive discussion among the analysis team and in consultation with the project's Community Advisory Council.

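### The contamination item records what a respondent passed on, not whether a participant with a component 'off' received that component's content

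*Protocol article*

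**What the plan says.** Randomization and masking (2.6) introduces the measure with the words "To measure possible contamination" and then describes it: "participants are asked on follow-up surveys the extent to which they discussed content received in their condition with participants randomized to other conditions". The same section says that teens and caregivers "are asked not to discuss their condition assignment with anyone outside of their group". The article describes no other contamination measure.

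Three other places fix what contamination would mean in this trial:

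- Study design (2.1): "All dyads of Latina teens and their female caregivers receive the first of the four intervention sessions". The other three sessions are each on or off, which gives eight conditions.
- Procedures (2.7): "All receive the constant component".
- Analyses (2.15): each factor is effect coded, +1 for on and −1 for off, so every component effect is an on-versus-off contrast.

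**The concern.** The conditions differ only in the three optional sessions. A component's contrast is diluted when someone with that component off receives its content from elsewhere. The item asks about the opposite flow. A participant without the Condoms and Contraception session who heard a full account of it from a friend can truthfully answer that she discussed none of her own content with anyone.

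Feasibility of the factorial design is one of the two primary aims, and the pilot is meant to inform a fully powered trial. Cross-condition contact is plausible, since any community partner organization (CPO) may deliver any condition and follow-up comes about 6 months later. The designers of the next trial will want to know whether the components stay separate, and which one leaks if they do not. The item as described does not supply that.

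**Working it through.** The protocol states no figure for contamination, so there is none to reproduce. The check sets the item beside the quantity it stands for.

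**1. Direction.** The item's object is content received in the respondent's own condition, and its flow is from her to others. Contamination of component j is content of j reaching a respondent with j off. By definition, j is not in her own condition's content, so the item as described does not ask about it.

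**2. Constant content.** Everyone has the constant session, so talk about it cannot contaminate. It still counts as content received in one's condition.

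**3. Gradient across the eight conditions.** These assumptions are not in the protocol: each respondent has one contact, drawn evenly from the other 7 conditions; each session's content is discussed with probability p, equal in all conditions; answers are truthful. With k optional sessions on:

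- item, constant counted = 1 − (1 − p)^(k+1)
- item, optional content only = 1 − (1 − p)^k
- true receipt = average over the other 7 conditions of 1 − (1 − p)^m, where m is the number of components off for the respondent and on for the contact

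Example for k = 0 and p = 0.10: of the other 7 conditions, 3 have m = 1, 3 have m = 2 and 1 has m = 3. Receipt = (3 × 0.10 + 3 × 0.19 + 0.271)/7 = 1.141/7 = 16.3%.

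Results at p = 0.10:

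| Optional sessions on | Conditions | Item, constant counted | Item, optional only | True receipt of off content |
|---|---|---|---|---|
| 0 | 1 | 10.0% | 0% | 16.3% |
| 1 | 3 | 19.0% | 10.0% | 11.1% |
| 2 | 3 | 27.1% | 19.0% | 5.7% |
| 3 | 1 | 34.4% | 27.1% | 0% |

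The orderings are opposite at every p tried (0.05, 0.10, 0.20, 0.30). At p = 0.05 the item (constant counted) reads 5.0, 9.8, 14.3 and 18.5% against receipt of 8.4, 5.6, 2.9 and 0%. At p = 0.30 it reads 30.0, 51.0, 65.7 and 76.0% against 44.1, 31.7, 17.1 and 0%.

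**4. Overall level at p = 0.10, all eight conditions weighted equally.**

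- Item, constant counted: (10.0 + 3 × 19.0 + 3 × 27.1 + 34.4)/8 = 22.8%
- Item, optional only: (0 + 3 × 10.0 + 3 × 19.0 + 27.1)/8 = 14.3%
- True receipt: (16.3 + 3 × 11.1 + 3 × 5.7 + 0)/8 = 8.3%

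So under these assumptions the pooled item does not understate total contamination. What it lacks is the location.

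**5. Possible dilution, illustrative only.** If a share f of off participants receives a share s of a component's content, and effect is proportional to content, the on-off difference shrinks by f × s. With assumed f of 10 to 30% and s of one half: 0.10 × 0.5 = 5% to 0.30 × 0.5 = 15%.

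**The case against.** The strongest reply is that the article paraphrases a survey item in one sentence and the questionnaire is not shown. Discussion is usually two-way, and the instrument may also ask about receipt. This stands as a limit: the point concerns the measure as the article describes it. If receipt questions already exist, the sponsor need only say so.

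A reader might also infer more than the documents support:

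- *That constant-only groups would report about zero.* They receive the Foundations session and can report talk about it. Zero follows only if the item excludes constant content, which is not stated.
- *That a low reading would be false reassurance.* Participants in every condition are asked, and talk between participants needs a sender. Truthfully low sending across the trial therefore implies limited receipt, apart from one sender reaching several people. Under-reporting could mislead, but a receipt question is self-reported too.
- *That answering means admitting a breach.* The request covers condition assignment, whereas the item asks about content.
- *That the inverse gradient is a property of the design.* It needs similar willingness to talk across conditions and answers that rise with the amount of content. Otherwise the item may read flat, and it still does not show receipt. No tabulation by the respondent's own condition is planned.

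Nor is the item wholly blind to component. A sender's condition is known, so a report from a group with one optional session on narrows what could have leaked. It does not identify the recipient, and with two or three optional sessions on it does not identify the component.

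**Conclusion.** The point holds in this limited form. As described, the item measures sending and not receipt by participants with a component off. It serves as a rough overall gauge of cross-condition talk, but it cannot show who was exposed or to which component. That conclusion follows from the item's stated object and needs none of the modelling assumptions. The tendency to read lowest where most components are off is conditional on the assumptions in the working, and the 5 to 15% dilution rests wholly on assumed inputs.

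The consequence is modest. The protocol calls the effectiveness analyses exploratory, says the pilot is not powered for them, and sets no contamination benchmark among its primary feasibility measures. This is an inexpensive improvement to what the pilot can tell the next trial, and it does not threaten the pilot's primary results.

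**What to change.** Keep the existing item. After the outcome items on the 6-month follow-up survey, add one question for each of the three optional components, asking whether the respondent heard or received that content from someone who attended another Floreciendo workshop. The respondent need not know the other person's condition: content of a component that was off for her must come from a condition where it was on.

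Report the proportion among participants with that component off, by component and, where numbers allow, by CPO. Each component is off in 4 of 8 conditions, so about 12 of the planned 24 workshops and 92 × 12/24 = 46 dyads. At the 70% follow-up benchmark that is 0.70 × 46 ≈ 32 dyads per component, or about 8 per CPO if spread evenly over four. The by-component figure is usable descriptively; the by-CPO figure will be thin.

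The cost is about three short questions on an existing questionnaire, with no change to randomization, sample size or delivery. The drawbacks are slight added burden, self-report recall over about 6 months, possible confusion with overlapping Foundations content, and missing answers from participants already followed up, which should be reported as such.
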